#### Intervention description {11a}

Patients will undergo spinal arthrodesis with a pedicle screw placement by posterior approach under general anaesthesia. The robot-assisted group will be operated using a spinal robot with integrated real-time 3D navigation (Mazor X Stealth Edition). All patients in the robot-assisted group will require a CT scan as part of preoperative assessment, to be used for surgical planning and intraoperative navigation. The conventional group will be operated using the freehand surgical technique with 2D fluoroscopy. Surgical access will be open or minimally invasive, depending on the investigating surgeon’s preference and the indication for surgery. Interbody fusion will be performed in selected cases, depending on the indication for surgery.

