### Outcomes {12}

The primary outcome of this study will be the rate of pedicle screws placed with grade A accuracy according to Gertzbein-Robbins classification (Table 1) in the robot-assisted versus conventional groups. The evaluation of the placement of the screws will be based on CT images from postoperative day 1 and will be carried out by two radiologists independent to the surgical team, blinded to the technique used for screw placement. In case of disagreement between the two evaluators, a 3rd evaluator will be requested.

**Table 1 Tab1:** Gertzbein-Robbins classification of pedicle screw placement

Grade A	fully intrapedicular position without breach of the pedicle cortex
Grade B	<2 mm cortical breach
Grade C	2-4 mm cortical breach
Grade D	4-6 mm cortical breach
Grade E	exceeding the pedicle cortex <6 mm or is outside of the pedicle

The secondary outcomes of the study will be as follows:Intervention time (min)OR occupancy time (min)LOS (days)EBL (volume of the suction jar at the end of the intervention in ml)Surgeon’s intraoperative radiation exposure (a dosimeter placed in contact with the surgeon’s clothing, in cGy/cm^2^)Signs of screw fracture/loosening (CT at 12 and 24 months postoperatively)Superior-level facet joint violation according to Babu-Mehta classification (Table 2; CT on postoperative day 1)Types of complications (neurologic, infectious, vascular, general, late and early mechanical complications) and complication rate at 24 months postoperativelyReoperation rate on the same instrumented level or one level above at 24 months postoperativelyFunctional and clinical outcomes at 3, 12 and 24 months postoperatively (pain on visual analogue scale [VAS; 0, best; 10, worst], ODI [0, best; 100, worst], HAD scale [0, best; 21, worst], sensory status with 3-point scale [0, absent sensation; 2, normal sensation], motor status with Medical Research Council’s [MRC] scale for muscle strength [0, no contraction; 5 full muscle strength])Cost-utility analysis based on medical costs and quality of life (QoL) evaluation (quality-adjusted life years [QALYs] derived from EuroQol [EQ-5D-5L questionnaire) at 12 months postoperatively

**Table 2 Tab2:** Babu-Mehta classification of facet joint violation

Grade 0	Screw not in facet
Grade 1	Screw in lateral facet but not in facet articulation
Grade 2	Penetration of facet articulation
Grade 3	Screw travels within facet articulation

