## Statistical methods

### Statistical methods for primary and secondary outcomes {20a}

The quantitative variables will be described by the number of values entered, the number of missing data, the mean, the standard deviation, the median, the 1st and 3rd quartiles, the minimum and the maximum. The qualitative variables will be described by the number of values entered, the number of missing data, the frequency, the percentage of each modality and the 95% confidence interval (CI) of each modality, if relevant. The type I error (*α*) is set at 5% with a two-tailed analysis for the entire study. No management of multiplicity will be carried out. The secondary outcomes will be analysed on an exploratory basis. The primary outcome (proportion of grade A placed screws according to Gertzbein-Robbins classification on postoperative day 1) will be described by group (robot-assisted vs. conventional surgery) and compared using a marginal logistic model (taking into account screw clusters in the same patient) including the group and the randomization stratification factor (long-segment fusion vs. short-segment fusion). The results of the marginal logistic model will be interpreted in terms of adjusted odds ratio (aOR) accompanied by the 95% CI. Intervention time, OR occupancy time, LOS, EBL and surgeon’s intraoperative radiation exposure will be described by group (robot-assisted vs. conventional surgery) and compared using an analysis of variance (ANOVA) including the group and the randomization stratification factor (long-segment fusion vs. short-segment fusion). Radiological stability (signs of screw fracture/loosening), superior-level facet joint violation, complication and reoperation rates will be compared using logistic regression including the group and the stratification factor of the randomization (long-segment fusion vs. short-segment fusion). Functional outcomes (ODI, pain, HAD) will be compared using an analysis of covariance (ANCOVA) including the group, the score at inclusion and the randomization stratification factor (long-segment fusion vs. short-segment fusion); this analysis will be carried out at each evaluation time (3-, 12- and 24-month follow-up). The evaluation of sensory status and motor status will be compared using a Cochran-Mantel-Haenszel test including the group and the stratification factor of the randomization (long-segment fusion vs. short-segment fusion); this analysis will be carried out at each evaluation time (3-, 12- and 24-month follow-up). The cost-utility analysis will be carried out according to the recommendations of the French National Authority for Health (HAS) [11], based on QALYs (lifespan weighted by health-related quality of life), derived from the EQ5D-5L. All direct medical costs will be measured over 12 months following hospital discharge. The incremental cost-utility ratio (difference in costs divided by the difference in QALYs) between robot-assisted surgery and conventional surgery will be determined at 12 months along with their 95% CIs. All statistical analysis will be performed using the latest version of the SAS software.

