## Discussion

According to most recent meta-analyses, freehand surgery with 2D fluoroscopy provides worse pedicle screw placement accuracy compared to robot-assisted surgery and computer-assisted navigation (CAN) [13–18], with robot-assisted surgery granting the best results [14, 19]. However, some meta-analyses have found comparable outcomes for freehand versus robot-assisted surgery [20–22].

During the last decade, four spinal robots with integrated CAN (ROSA ONE Spine, ExcelsiusGPS, Mazor X Stealth Edition, TiRobot) have been introduced into the market, allowing for surgical planning, guidance, and real-time 3D navigation [2]. Of these four robots, only TiRobot (TINAVI) has been evaluated in RCTs [3, 23–25], providing excellent outcomes, although this robot is uniquely available on the Chinese market. Furthermore, two recent meta-analyses have suggested the advantage of integrating CAN into a robotic system [21, 26]. Therefore, it is important to further investigate the combination of these two technologies. Additionally, there is a scarcity of evidence concerning the economic aspect of using spinal robots, both during the intervention and in the first 12 months following hospital discharge. The latter could include painkiller consumption, work incapacity, readmissions and revisions. The present RCT will provide high-quality clinical data concerning the Mazor X Stealth Edition and will deliver a cost-utility analysis.

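### The cost window starts at hospital discharge, so the cost-utility ratio leaves out the index-episode costs that allocation changes most directly

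*Protocol article*

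**What the plan says.** Four places in the protocol article bear on the cost side of the economic analysis.

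- **Statistical methods {20a}** sets the window: "All direct medical costs will be measured over 12 months following hospital discharge". The next sentence defines the estimate: "The incremental cost-utility ratio (difference in costs divided by the difference in QALYs) between robot-assisted surgery and conventional surgery will be determined at 12 months". The same section says that the HAS recommendations will be followed.
- **Outcomes {12}** lists a "Cost-utility analysis based on medical costs and quality of life (QoL) evaluation", with QALYs from the EQ-5D-5L, to be assessed "at 12 months postoperatively".
- **Data collection {18a}** has one e-CRF item for medical costs, tied to the 12-month follow-up, with no start point. The participant timeline places that visit at D0 + 360 days, D0 being the day of surgery.
- **Discussion** describes the evidence gap on the economics of spinal robots as "both during the intervention and in the first 12 months following hospital discharge", and says that this trial will deliver a cost-utility analysis.

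Two further facts matter. Intervention description {11a} states: "All patients in the robot-assisted group will require a CT scan as part of preoperative assessment". No such requirement is stated for the conventional arm. Operating-room occupancy and length of stay are collected, but they appear only as separate secondary outcomes compared by ANOVA, never as inputs to cost.

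**The concern.** An incremental cost-utility ratio is meant to weigh the extra cost of one strategy against its extra health gain. Here the two strategies differ in what happens before discharge: the robot is used or not, a planning CT is required or not, and time in the operating room and in the bed may differ. A cost clock that starts at discharge sees none of this. It records only downstream differences such as readmissions and revisions.

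The ratio would then be presented as the cost-utility of robot-assisted against conventional surgery while its numerator lacks the incremental cost of the technology under test. If post-discharge costs happened to be equal in the two arms, the ratio as written would be zero whatever the robot costs and however much the stay changes. It could not support the statement about overall cost of care that the abstract names as a potential benefit.

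**Working it through.** The documents state no cost, QALY or ratio figure, so there is nothing to reproduce. The check has two parts.

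**1. The passages side by side.**

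| Section | Start of costs | End of costs |
|---|---|---|
| Statistical methods {20a} | hospital discharge | 12 months after discharge |
| Outcomes {12} | not stated | 12 months after surgery |
| Data collection {18a} | not stated | 12-month visit (D0 + 360 days) |
| Discussion (the economic question) | the intervention | 12 months after discharge |

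Only the first row gives an operative rule for the start, and it covers only the second half of the question in the last row. No section says that index-admission costs will be added.

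**2. Sign and size of what is left out.** Per patient, robot minus freehand, the omitted difference is

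omitted = R + ΔT × c_T + ΔL × c_L + CT

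where R is robot cost per case, ΔT the difference in operating-room minutes, c_T the cost per minute, ΔL the difference in days of stay, c_L the cost per day, and CT the cost of the preoperative scan. Every value below is an assumption, because the article supplies none:

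- R = 500, 1,500 or 3,000 euros
- ΔT = -15, 0 or +30 min, at c_T = 10 or 15 euros per min
- ΔL = 0, -1 or -2 days, at c_L = 500 or 1,000 euros per day
- CT = 100 or 200 euros

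This gives 3 × 3 × 2 × 3 × 2 × 2 = 216 combinations.

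- Lowest: 500 - 15 × 15 - 2 × 1,000 + 100 = **-1,625 euros**
- Highest: 3,000 + 30 × 15 + 0 + 200 = **+3,650 euros**
- Negative in 42 combinations; positive or zero in the other 174

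The grid shows that both signs are possible. The count is not a probability, since the grid points were chosen and carry no weights.

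Reduction in stay that cancels the other omitted items, taking CT = 150 and c_T = 10:

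- R = 500, ΔT = 0: (500 + 150) / 1,000 = 0.65 days, or 650 / 500 = 1.3 days
- R = 3,000, ΔT = 30: (3,000 + 300 + 150) / 1,000 = 3.45 days, or 3,450 / 500 = 6.9 days

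Effect on the ratio, as omitted difference divided by an assumed QALY gain:

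| Omitted (euros) | gain 0.01 | gain 0.02 | gain 0.05 |
|---|---|---|---|
| +1,500 | +150,000 | +75,000 | +30,000 |
| -1,000 | -100,000 | -50,000 | -20,000 |

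A modest omission per patient therefore moves the ratio by tens of thousands of euros per QALY in either direction.

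**The case against.** The best defence is that the sentence is loosely worded and is not a decision to exclude the index episode. It does not say that pre-discharge costs are left out. The outcome list speaks of medical costs without restriction, the e-CRF item has no start at discharge, the Discussion includes the intervention, and HAS recommendations are to be followed. A full protocol or analysis plan may itemise the costs, and such detail is commonly left to it.

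Part of this stands. The intention may well be broader than the wording, and the absence of a cost itemisation is no fault in an article. But the start point is a stated rule. A general reference to recommendations whose content is not in the document does not override the specific sentence beside it, and the more inclusive passages show the conflict without resolving it.

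A reader might infer something stronger: that the ratio must come out wrong in favour of the robot, because the robot's price is never counted. The documents do not support that. The abstract and the Introduction anticipate a shorter stay with robotic surgery, and omitting a shorter stay counts against the robot. No sign is given for the difference in operating-room time. A net bias towards the robot is plausible, but it is not established.

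A reader might also make much of costs and QALYs running on different clocks. At the far end, the mismatch between 12 months after discharge and 12 months after surgery is about the length of the index stay. The material loss is at the start of the window.

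**Conclusion.** The sentence that fixes the cost window is wrong as written. Followed literally, it removes the costs most directly changed by allocation, cannot answer the economic question in the Discussion, and does not match the 12-month postoperative horizon of the outcome list. The resulting ratio would be biased in a direction that the documents do not fix.

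The size depends entirely on assumed unit costs and an assumed QALY difference, so the figures above show only that the effect can be large and of either sign. The firm part of the conclusion, that the passages conflict and the numerator is incomplete, needs no assumed cost.

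This should be corrected, but it does not threaten the trial's main result. Cost-utility is a secondary outcome analysed on an exploratory basis. The primary outcome, sample size and randomisation are unaffected.

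**What to change.** Replace the cost-window sentence in Statistical methods {20a} with one to this effect: direct medical costs will be measured from the preoperative work-up, through the index admission, to 12 months after surgery (D0), including the preoperative CT, robot use, operating-room time and length of stay; QALYs will be calculated over the same 12-month postoperative horizon. Align Outcomes {12}, the e-CRF cost item and the Discussion with it.

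Make the change before any cost comparison is seen, because a window chosen afterwards would be hard to defend.

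The cost is small. Operating-room occupancy and length of stay are already recorded for each patient. What has to be added is hospital accounting data to price them, together with a cost per case for robot use and for the preoperative CT. The robot's economic result may look better or worse than under the current wording.

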**Discussion:**

This RCT will provide insight into whether robot-assisted surgery with the newest generation spinal robot yields better pedicle screw placement accuracy than freehand surgery. Potential benefits of robot-assisted surgery include lower complication and revision rates, shorter length of stay, lower radiation exposure and reduction of economic cost of the overall care.

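### The only named cost-utility result is a ratio with a 95% CI, which cannot be read if the QALY difference is not clearly away from zero; report both differences and net monetary benefit instead

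*Protocol article*

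**What the plan says.** All of this stands in the protocol article, section {20a}, unless another place is named.

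- The result: "The incremental cost-utility ratio (difference in costs divided by the difference in QALYs) between" the two arms, with the sentence ending "robot-assisted surgery and conventional surgery will be determined at 12 months along with their 95% CIs". How the interval is built is not stated.
- The inputs: the analysis is "based on QALYs (lifespan weighted by health-related quality of life), derived from the EQ5D-5L", and "All direct medical costs will be measured over 12 months following hospital discharge".
- The guidance: "The cost-utility analysis will be carried out according to the recommendations of the French National Authority for Health (HAS").
- The status: "The secondary outcomes will be analysed on an exploratory basis".
- The abstract's discussion allows for a saving: "Potential benefits of robot-assisted surgery include lower complication and revision rates, shorter length of stay, lower radiation exposure and reduction of economic cost" of care.

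The section mentions no separate analysis of the two differences, no net monetary benefit, no cost-effectiveness plane, no acceptability curve and no value per QALY. The sample size in section {14} is set on grade A screws.

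**The concern.** The economic question is whether the QALYs gained are worth the extra cost. A ratio answers it only when the sign of its denominator is known.

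Two difficulties follow. First, the ratio discards the signs: opposite results can give the same negative number. Second, when the data do not settle the sign of the QALY difference, a ratio CI stops behaving like an ordinary interval. Because the abstract names lower cost as a possible benefit, a negative ratio is an outcome that the authors themselves consider possible.

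At stake is whether the reader of the economic result can tell what its error bars mean. The primary outcome and the sample size are not affected.

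**Working it through.** **1. The plan's own figure.** No figure is stated for the cost-utility analysis. The screw calculation in {14} reproduces. For 88% against 95%, two-sided 5% and 90% power, the number is 332 per group (pooled variance) or 328.3 (unpooled). The design effect is 1 + (5 - 1) × 0.3 = 2.2, which gives 730 or 722 screws against the stated 725. Of 150 patients per group, 5% not operated leaves 150 × 0.95 = 142.5, taken below as 143 (142 in step 5).

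**2. Sign ambiguity (no assumption about variability).** Robot saves 1,000 and gains 0.05 QALY: -1,000 / 0.05 = -20,000. Robot costs 1,000 more and loses 0.05 QALY: 1,000 / (-0.05) = -20,000. The conclusions are opposite and the ratio is the same.

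**3. When the ratio interval breaks down.** Write ΔC and ΔQ for the estimated differences. Fieller's 95% set holds every value λ with (ΔC - λΔQ)² ≤ 1.96² × Var(ΔC - λΔQ). The coefficient of λ² is ΔQ² - 1.96² × SE(ΔQ)². If it is negative, which means that the 95% CI for ΔQ includes zero, the set is unbounded.

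For a true difference δ, the chance of this is Φ(1.96 - δ/SE) - Φ(-1.96 - δ/SE), with SE = SD × √(2/143) = SD × 0.118. Example: δ = 0.02 and SD 0.20 give SE 0.0237 and δ/SE = 0.845, so Φ(1.115) - Φ(-2.805) = 0.865.

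The QALY SDs and differences are assumptions, because the document gives none:

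| QALY SD | CI half-width | δ = 0 | 0.02 | 0.03 | 0.05 | 0.08 |
|---|---|---|---|---|---|---|
| 0.10 | 0.023 | 95% | 61% | 28% | 1% | 0% |
| 0.15 | 0.035 | 95% | 80% | 61% | 20% | 0.5% |
| 0.20 | 0.046 | 95% | 86% | 75% | 44% | 8% |
| 0.25 | 0.058 | 95% | 90% | 83% | 61% | 23% |

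With 120 per arm, for instance after loss of questionnaires, the ranges over the same SDs are 66-90% at 0.02 and 3-66% at 0.05.

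**4. What percentile limits do.** A normal simulation assumed a cost difference of 1,000 and a cost SD of 5,000, with 143 per arm. At a QALY difference of 0.02 and SD 0.20, the 2.5th and 97.5th percentiles of the ratio are about -458,000 and +509,000. Of the draws, 3.6% have the robot cheaper and better and 19% have it dearer and worse; both groups lie on the negative side. At 0.05 and SD 0.10 the percentiles are about -3,300 and +54,000, almost no draws have the robot dearer and worse, and the interval can be read.

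**5. Comparison with net monetary benefit.** Net benefit is λΔQ - ΔC. Assume λ = EUR 50,000, cost SD EUR 6,000, no correlation, 142 per arm, and a robot that is EUR 1,500 cheaper with +0.02 QALY. The expected net benefit is 50,000 × 0.02 + 1,500 = 2,500. The SE of ΔC is 6,000 × √(2/142) = 712.

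| QALY SD | SE of 50,000 × ΔQ | SE of net benefit | Ratio to SE | Chance that its CI excludes 0 | Chance that the ratio's upper percentile limit is below 50,000 (2,000 simulated trials) |
|---|---|---|---|---|---|
| 0.15 | 890 | 1,140 | 2.19 | 59% | 18.8% |
| 0.20 | 1,187 | 1,384 | 1.81 | 44% | 14.1% |
| 0.25 | 1,483 | 1,645 | 1.52 | 33% | 11.2% |

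By the definition in step 3, Fieller's set is exactly the set of λ at which the 95% CI for net benefit includes zero. With Fieller's method the gap in this table therefore vanishes. It belongs to percentile limits alone.

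**The case against.** The strongest case against the point has five parts.

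- **Deference to HAS.** The display of uncertainty may be fixed in those recommendations, which are not available here. This stands as a limit: the full plan may already contain the better displays. It does not change the fact that {20a} names one result and puts the CI on it.
- **A condensed article.** Planes, curves and thresholds are usually left to an analysis plan, so their absence alone is no finding. That is right. The point concerns the method that is stated.
- **The plural.** The word their before CIs may cover the two separate differences, which would show the signs. The reading is possible, but the sentence reports the ratio as the result. If the differences were meant, the text should say so.
- **Frequency.** A reader might infer that the interval will often be uninterpretable. The document does not support this, because over the assumed inputs the chance runs from under 1% to 95%, and the 95% at a zero difference is simply 1 minus α.
- **Loss of information.** A reader might infer that the ratio CI necessarily hides evidence, or makes a dearer and worse robot look like good value. The protocol specifies neither percentile limits nor a threshold rule, and Fieller's set carries the same information as net benefit. An unbounded set is an honest sign that the QALY sign is unresolved.

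**Conclusion.** The point holds as a moderate improvement to an exploratory secondary analysis. The sign ambiguity, and the failure of the ratio interval when the QALY difference is not clearly away from zero, follow from the definition in {20a} without assumptions about variability.

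How likely the failure is cannot be taken from the document. It is more likely than not for true differences up to 0.02 at every SD examined, and unlikely for 0.05 or more when the SD is small. Any loss against net benefit depends on percentile limits being used and on the assumed costs, correlation and value per QALY.

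It would go too far to say that the trial's economic conclusion rests on this interval or is invalid. The analysis is labelled exploratory, no decision rule is stated, and the HAS guidance may add other displays.

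**What to change.** In {20a}, replace the ratio with its CIs by the following:

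1. Report the cost difference and the 12-month QALY difference, each with a 95% CI.
2. Express uncertainty through incremental net monetary benefit (value per QALY × QALY difference - cost difference) with its 95% CI, over a stated range of values per QALY.
3. Show the joint bootstrap distribution on the cost-effectiveness plane, with the acceptability curve.
4. Give the ratio as a point estimate when both differences share a sign, and say which sign. Otherwise state which arm dominates.
5. If a CI on the ratio is kept, use Fieller's method and give it only when the QALY difference is clearly away from zero.

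If the full plan or the HAS-based methods already provide this, one sentence in {20a} saying so is enough.

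The cost is a wording change and a few lines of code on data already to be collected, with no change to the sample size. The small downside is that the result is shown over a range of values per QALY instead of as one ratio. The change should be made before the results are seen.
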